#### Participation

The Young Children's Participation and Environment Measure (YC-PEM) will be used to assess participation in three settings: home, daycare/preschool, and the community [31]. This questionnaire, completed by a parent or caregiver, was developed for children aged 0–5 years. The YC-PEM will be administered at baseline and every three months throughout the twelve-month study period and may be administered over the phone with research staff or via online self-report through REDCap.

#### Spasticity

We will use a newly developed device for measuring spasticity called the Portable Spasticity Assessment Device (PSAD, Nordic Neurostim, Denmark) [32, 33] to determine if the intervention reduces contracture or spasticity at the ankle, as seen in other active therapies for the lower extremities [32, 34]. Ankle joint range of motion, mechanical resistance caused by contracture and reflex-mediated spasticity can be measured using this device. We focus on the ankle, since this is the lower extremity joint very commonly affected by spasticity and is often the target of passive approaches including botulinum toxin, serial casting and orthoses [35]. Contracture, defined here as increased stiffness in joint movement cause by changes in intrinsic soft-tissue properties, will be reflected by the torque during slow stretch without any muscle activity. Spasticity will be indicated by the joint angle at which reflex EMG is generated in a fast stretch, similar to the angle of catch in the Tardieu Scale. This measure will be used at two study sites, because we only have two devices.

#### Reporting of co-interventions

During the six-month control period for the Waitlist-control Group and the follow-up period for both groups, parents will be asked to report any rehabilitation for their child’s lower extremity including the nature, duration and frequency. This will provide clarity on usual care, and the variations between sites.

### Sample size

The effect size on the primary outcome measure is estimated at 0.91, based on data from a cohort of children trained by their parents in our preliminary efficacy trial, as this is the more conservative estimate compared to the 1.67 effect size of children trained by a physical therapist. Twenty children per group are required to achieve statistical power of 0.8 and significance of 0.05. To account for cluster randomization with an estimated intra-cluster correlation coefficient of 0.02, a design effect of 1.4 is considered, which results in a total sample size of 56.

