## Methods

### Experimental design

This is a three-centre (Edmonton [primary site], Calgary, and Ottawa), mixed methods study in which a qualitative study is embedded in a waitlist-control, single-blind randomized controlled trial (RCT). The children will be randomly allocated to either the Immediate Intervention Group (treatment) or the Waitlist-control Group (usual care) with follow-up (Fig. 1). The Immediate Intervention Group will undergo the three-month ELEVATE intervention immediately following randomization. The Waitlist-control Group will delay treatment for six months before initiating the ELEVATE intervention. The primary time point of interest is at six months in the study (Fig. 2). All children will undergo monthly assessments for 12 months in the study and will also be assessed at age four years of age to evaluate longer-term effects of training.

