### Randomization and stratification

Participants will undergo baseline assessments before randomization (Fig. 1). The randomization sequence was generated in Edmonton by a statistician. We used a permuted block design with a block size of 2–4. Randomization was stratified by city to ensure that the numbers allocated to the intervention and control groups will be roughly equal at each site. Their assignment is concealed until baseline assessments are complete, and are made available to the study sites through Research Electronic Data Capture (REDCap).

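### The sample size is raised from 40 to 56 for cluster randomisation, but the trial randomises individual children within city, so the stated reason for the extra 16 does not hold

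*Protocol article*

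**What the plan says.** All references are to the protocol article.

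- **Sample size**, starting assumption: "The effect size on the primary outcome measure is estimated at 0.91".
- **Sample size**, uninflated requirement: "Twenty children per group are required to achieve statistical power of 0.8 and significance of 0.05". That is 40 children.
- **Sample size**, inflation: "To account for cluster randomization with an estimated intra-cluster correlation coefficient of 0.02, a design effect of 1.4 is considered". The section gives 56 children as the outcome, and no other step leads there from 40.
- **Experimental design**, unit of allocation: "The children will be randomly allocated to either the Immediate Intervention Group (treatment) or the Waitlist-control Group (usual care". On sites: "This is a three-centre (Edmonton [primary site], Calgary, and Ottawa), mixed methods study".
- **Randomization and stratification**: "We used a permuted block design with a block size of 2–4", and "Randomization was stratified by city to ensure that the numbers allocated to the intervention and control groups will be roughly equal at each site".
- **Data management and analysis** compares change from baseline to six months between the two groups.
- **Cost-effectiveness analysis** uses regression at participant level, with study site among the covariates.

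**The concern.** The Sample size section names a unit of randomisation that appears nowhere else in the article. Cluster randomisation means that whole groups (sites, clinics, therapists) are assigned to an arm. Permuted blocks of children within city, with arms balanced at each city, make the city a stratum. These two descriptions cannot both be true.

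The unit of randomisation and the basis of the sample size are core design statements. The cluster rationale is the only ground given for 16 of the 56 children. It also governs how the margin is read. Taken literally, the 16 are used up by clustering and 56 children carry the information of 40. Under the design described, all 56 count in full. The two readings give different answers on the trial's power and on how much loss it can absorb.

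**Working it through.** **Inputs from the Sample size section:** effect size d = 0.91 (difference divided by SD), power 0.80, significance 0.05, 20 per group, ICC 0.02, design effect 1.4, total 56. **From Experimental design and Randomization and stratification:** three sites, individual allocation, roughly equal arms within city. Sidedness is not stated. I took two-sided, because it reproduces the plan's figure and one-sided does not (15.65 per group by t-test).

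**1. Reproduce the plan's figures.**
- Normal approximation: n = 2(1.96 + 0.8416)² / 0.91² = 18.96, so 19 per group.
- Two-sided t-test: n = 19.96, so 20 per group, with power 0.801 at 20.
- Inflation: 40 × 1.4 = 56.

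The stated figures reproduce.

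**2. Where 1.4 could come from.** The usual formula is DE = 1 + (m − 1) × ICC.
- Exactly 1.4 needs m = 1 + 0.4/0.02 = 21 children per cluster.
- Three sites sharing 56 children give m = 56/3 = 18.7 and DE = 1 + 17.67 × 0.02 = 1.353, which is 1.4 to one decimal.
- Unrounded, 20 × 1.353 = 27.07 per group. Rounded up this is 28, again 56 in total.

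The factor is thus compatible with treating the three cities as clusters.

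**3. Does that factor apply?** Write a child's outcome as site effect + treatment effect + individual error. Where both arms are at the same site in about equal numbers, the site effect enters both arm means alike and drops out of their difference. What remains is the within-site variance, (1 − ICC) times the total. If 0.91 is scaled to the total SD and site is in the model, the multiplier is 0.98 (40 × 0.98 = 39.2) rather than 1.4. For practical purposes the requirement is 40.

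**4. What 56 delivers under the design described** (two-sided t-test, d = 0.91, 1:1, losses split evenly; the loss rates are assumed, since the article gives none):

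| Loss | Children per group | Power |
|---|---|---|
| 0% | 28 | 0.917 |
| 10% | 25.2 | 0.886 |
| 20% | 22.4 | 0.845 |
| 28.6% (16 of 56) | 20 | 0.801 |
| 30% | 19.6 | 0.792 |

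With 28 per group, 80% power is reached at d = 0.762.

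**5. Could therapist clustering justify 1.4?** Only the ELEVATE arm is grouped by study therapist up to six months, so average the factor over the arms: [1 + (1 + (m − 1) × 0.02)] / 2. Caseloads are not given, so m is an assumption.

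| Children per therapist (assumed) | Average factor | Total for 80% power |
|---|---|---|
| 2 | 1.01 | 40.4 |
| 5 | 1.04 | 41.6 |
| 10 | 1.09 | 43.6 |
| 28 (one therapist for the whole arm) | 1.27 | 50.8 |

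No caseload reaches 1.4 at the stated ICC.

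**The case against.** The best defence is that nothing is miscalculated and nothing is put at risk. The 0.80 is attached to 20 per group and is right there; the article states no power for 56. The factor can be recovered from three sites after rounding. The planned comparisons are between groups of children, and the cost-effectiveness regression already treats the child as the unit and adjusts for site, so there is no sign that anyone intends a cluster analysis. Treatment is delivered by therapists in several public and private centres, so some clustering in the treated arm is plausible and a cautious team might want a margin for it.

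Most of this stands, and it limits the point. A reader might infer that the stated power is wrong, that 1.4 cannot be reconciled with the trial's numbers, or that the trial is too small. The article supports none of these. A reader might also infer that the 16 extra children were really meant to cover dropout. The article does not say so, and the absence of an attrition rate from a condensed article is not a fault.

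The defence does not rescue the sentence itself. It gives cluster randomisation as the reason, not therapist effects, and therapist effects at ICC 0.02 would not produce the factor used. Treatment effects that differ between sites could add variance, but the section does not invoke that either.

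**Conclusion.** The point holds as a contradiction in the justification. The design effect of 1.4 rests on a feature the trial does not have, so the move from 40 to 56 is not justified by the reason given. The size is about 12 percentage points of power: about 92% at 56 with complete data, against the 80% that the inflation implies. Put another way, the detectable effect at 80% power is about 0.76 rather than 0.91. The direction is conservative.

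This rests on a two-sided t-test, 1:1 allocation, the article's own effect size, a site effect common to both arms, and no material clustering by therapist. The tolerance of 16 losses also assumes that they fall evenly on the two arms and are unrelated to outcome.

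**What to change.** Replace the cluster-randomisation sentence in the Sample size section. The new text should state that:

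- children are individually randomised, stratified by city;
- 40 evaluable children (20 per group) give 80% power for an effect size of 0.91, two-sided 0.05;
- 56 are enrolled, which gives about 92% power with complete data and at least 80% if up to 16 (28.6%) are lost evenly across arms.

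Include site, as the stratification factor, in the primary comparison, as the cost-effectiveness regression already does.

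Alternatively, if clustering by therapist in the ELEVATE arm was the intended reason, name it, give the expected caseload, use a factor that matches it (about 1.01 to 1.09 averaged over arms for assumed caseloads of 2 to 10 at ICC 0.02), and carry a therapist term into the analysis. The rest of the margin above 40 would then need its own stated purpose.

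The cost is one reworded paragraph and one covariate. Enrolment does not change.

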### Data management and analysis

Data will be entered in REDCap and analyzed at the primary study site. The primary time point of interest is at six months (Fig. 2), so change scores from baseline to six months will be compared between the ELEVATE intervention and control groups. Multiple linear regression models may be developed to assess the effect of variables (e.g. age at time of intervention) for each outcome. We will assess model fit and provide estimates with 95% confidence intervals.

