## Outcomes

### Primary outcome measure

#### Gross motor function

The Gross Motor Function Measure-66 (GMFM-66) is the primary outcome measure, a criterion-referenced observational measure for assessing gross motor function in children with CP [24]. It has been validated for children > 0.5 years old and is a gold standard for measuring gross motor function in children with CP [25]. The assessing therapists will be pediatric physical therapists from the community trained by study personnel to administer the GMFM-66 and are masked to the child’s group assignment. All parents will be informed not to disclose the child’s group assignment to the assessing therapist. All assessments will be videotaped for reference. The GMFM-66 will be administered twice at baseline and monthly thereafter, for a total of 14 measurements per child. The two measures at baseline will be averaged to provide a more reliable estimate.

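### The primary comparison is a two-point change score on an outcome measured monthly, so as written a child without a six-month score contributes nothing and earlier scores give no protection against informative loss

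*Protocol article*

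**What the plan says.** The protocol article's section on data management and analysis for the trial states the primary comparison of the two randomised arms in one sentence: "The primary time point of interest is at six months (Fig. 2), so change scores from baseline to six months will be compared". The next sentence adds a conditional regression: "Multiple linear regression models may be developed to assess the effect of variables (e.g. age at time of intervention) for each outcome". That regression is optional, is aimed at covariate effects, and is not described as longitudinal.

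The primary outcome section sets a much denser schedule: "The GMFM-66 will be administered twice at baseline and monthly thereafter, for a total of 14 measurements per child". The two baseline scores are averaged.

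The sample size section says "Twenty children per group are required to achieve statistical power of 0.8 and significance of 0.05", and then "a design effect of 1.4 is considered, which results in a total sample size of 56".

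**The concern.** A change score from baseline to six months exists only if the six-month score exists. Taken literally, the stated comparison leaves out a child who was scored at months 1 to 5 and missed month 6, although the trial has already collected the data that say most about where that child was heading.

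Two things are at stake. The first is precision: a trial of 56 children has little to spare. The second is validity. If children who are progressing poorly (or well) by month 5 are more likely to miss month 6, those with a six-month score are a selected group. A two-point comparison cannot correct for this. A likelihood-based model that includes the earlier scores can, provided the missingness depends only on scores that were observed and on covariates in the model. Before month 6 the trial's training load (one hour, four days a week, for 12 weeks) falls on the Immediate group alone, so loss related to progress in one arm is plausible. The article reports nothing that would establish it.

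**Working it through.** **Schedule.** Two baseline scores plus 12 monthly scores make 14, which matches the stated total. Months 1 to 5 therefore give five post-baseline scores before the primary time point. The waitlist group starts training only after six months, so months 1–6 are a clean comparison of ELEVATE with usual care.

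**The plan's own figure.** For a standardised effect of 0.91, two-sided alpha 0.05 and power 0.80, a two-sample t-test needs 19.96, so 20 per group (power 0.801). Then 2 × 20 × 1.4 = 56. The plan's total is reproduced.

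**Precision.** Let m be the proportion missing month 6 (assumed) and R² the share of six-month variance, after baseline adjustment, that the earlier scores explain (assumed). Variance relative to complete data is:

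- two-point comparison: 1/(1 − m)
- likelihood-based model using earlier scores: R² + (1 − R²)/(1 − m)

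A correlation of 0.8 between months 5 and 6 gives R² = 0.64, and 0.9 gives R² = 0.81. These two rows assume that every child missing month 6 has month 5 observed. R² = 0.30 stands for children who leave early or whose earlier scores predict poorly. At m = 0.15, 1/(1 − m) = 1.176:

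| Method | Calculation | Relative variance | Effective N (56 ÷ variance) |
|---|---|---|---|
| Two-point | 1/0.85 | 1.176 | 47.6 |
| Model, R² 0.30 | 0.30 + 0.70 × 1.176 | 1.124 | 49.8 |
| Model, R² 0.64 | 0.64 + 0.36 × 1.176 | 1.064 | 52.7 |
| Model, R² 0.81 | 0.81 + 0.19 × 1.176 | 1.034 | 54.2 |

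At m = 0.20 the relative variances are 1.25 (two-point), 1.175 (R² 0.30), 1.09 (R² 0.64) and 1.048 (R² 0.81).

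**Power at 15% loss.** Keeping the plan's 1.4 design effect, n per arm is effective N ÷ 2.8. This gives power of 0.73 for the two-point comparison, against 0.75 (R² 0.30), 0.775 (R² 0.64) and 0.79 (R² 0.81). Without the design effect, the same four figures are 0.87, 0.88, 0.90 and 0.91.

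**Bias, one illustration (all inputs assumed).** In the Immediate arm, 30% of children in the lower half by month-5 score and 10% in the upper half miss month 6. No control child does. The retained fraction is 0.5 × 0.7 + 0.5 × 0.9 = 0.8. Half-normal means are ∓0.798 SD, so the retained children's mean month-5 score is shifted by (0.45 − 0.35) × 0.798 ÷ 0.8 = 0.10 SD. Multiplying by a correlation of 0.8–0.9 gives a shift of 0.08–0.09 SD at month 6, which is 9–10% of the planned 0.91. Here missingness depends only on observed month-5 scores, so a correctly specified model on months 1–6 is not biased by it.

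**The case against.** **No complete-case rule is stated.** A reader might infer that the plan prescribes a complete-case analysis. It does not. The article names no test, analysis set or missing-data rule, and an unseen SAP could add imputation or a longitudinal model. This stands, and the absence of such text is no fault in a condensed article. What remains is the method the article does name: a two-point change score that makes no use of the monthly scores.

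**The favourable figures are a best case.** A reader might infer that the earlier scores carry most of the missing information. The documents give no correlation to support that. If burden drives loss, children may leave during the 12 weeks of training with only early scores, and the gain shrinks to the R² 0.30 row. This stands, so the range has to be shown.

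**Unequal loss alone does not bias the comparison.** Missingness must also relate to outcome within an arm. This stands. The article also gives reasons to expect retention: children tolerated this training in the preliminary trial, parents agree to the schedule at entry, and waitlisted families are offered the intervention after six months. Bias is a possibility, not a prediction.

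**Power may not be tight.** A reader might infer that the trial becomes underpowered. The 1.4 factor is attributed to cluster randomisation, yet the article describes allocation of individual children stratified by city. If the factor is unnecessary, 56 children give power of about 0.92, and 0.87 after 15% loss. This softens the precision argument and leaves the bias argument untouched.

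**The remedy is a matter of taste.** A two-point comparison is conventional, and with complete data the model gives essentially the baseline-adjusted month-6 result. True, but the benefit arises precisely when data are incomplete.

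**Conclusion.** The point holds in a limited form. The stated comparison discards five scheduled post-baseline scores. It is therefore less precise than it need be when month 6 is missed, and unprotected if missingness depends on those scores. At an assumed 15% loss its variance rises 18%, against about 3–6% for a repeated-measures model when month 5 is observed with a correlation of 0.8–0.9, and about 12% when earlier scores explain 30% of the variance. Every one of these sizes rests on an assumed loss rate and correlation.

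The total of 56 comes from the design effect alone, so it includes no stated attrition allowance. A reader might take that as part of this finding. It is a separate sample-size point: the model recovers only part of the loss and does not supply an allowance. The change is worth making but is not critical.

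**What to change.** Keep the group difference at six months as the estimand and say so. Estimate it from a mixed model for repeated measures on months 1–6, with group-by-month, baseline-by-month, age at randomisation and site as fixed effects. Site is the stratification factor, and site, age and baseline GMFM-66 are already the covariates named for the cost-effectiveness regressions. Include every randomised child with any post-baseline score.

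Pre-specify the covariance structure and the fallback, for example unstructured, then heterogeneous autoregressive if it does not converge, with small-sample degrees of freedom such as Kenward–Roger. These particular choices are negotiable. Using the monthly scores is the substance.

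The cost is SAP wording and a little programming, with no new visits or data. The downside is a covariance model in 56 children: an unstructured matrix over six visits has 6 × 7 ÷ 2 = 21 parameters, which is why the fallback must be fixed in advance. Children with no post-baseline score still contribute nothing, and any attrition allowance has to be settled separately in the sample size section.

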### Cost-effectiveness analysis (CEA)

In the CEA, the ratio of the difference in mean cost between the ELEVATE and Waitlist-control groups to the difference in effectiveness scores (change in GMFM-66) between groups will be used to estimate an incremental cost-effectiveness ratio (ICER) from the publicly funded healthcare payer and societal perspectives. The mean effectiveness for each group will be compared using patient level regression. We will use Ordinary least squares (OLS) to assess the difference in effectiveness and the difference in cost between groups. We will control for a set of covariates including study site, age and baseline GMFM-66 scores. The mean cost per participant for each group will also be compared using participant-level regression. A bootstrapped analysis will be conducted for the CEA and results presented on a cost-effectiveness acceptable curve (CEAC).

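### The primary GMFM-66 analysis is a change-score comparison with only optional, unfixed covariate adjustment, while the cost-effectiveness analysis commits to adjusting change in the same measure for site, age and baseline

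*Protocol article*

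**What the plan says.** **Primary analysis.** In the quantitative *Data management and analysis* section, the article names six months as the time point of interest, "so change scores from baseline to six months will be compared between the ELEVATE intervention and control groups". It names no test and commits to no covariate. The next sentence leaves modelling open: "Multiple linear regression models may be developed to assess the effect of variables (e.g. age at time of intervention) for each outcome". Neither baseline GMFM-66 nor site is mentioned there.

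**Cost-effectiveness analysis.** The denominator of the cost-effectiveness ratio is the "difference in effectiveness scores (change in GMFM-66) between groups", estimated by ordinary least squares. Here the commitment is firm: "We will control for a set of covariates including study site, age and baseline GMFM-66 scores". No time point is given for this change.

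**Design.** "Randomization was stratified by city"; neither age nor baseline function is a stratification factor. Entry is open from 8 months to 3 years of age. GMFM-66 is measured twice before randomisation: "The two measures at baseline will be averaged to provide a more reliable estimate".

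**Sample size.** "The effect size on the primary outcome measure is estimated at 0.91", and "Twenty children per group are required to achieve statistical power of 0.8 and significance of 0.05". A design effect of 1.4 takes the total to 56.

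**The concern.** The investigators have named the covariates they consider relevant to change in GMFM-66. They commit to them in the economic analysis but not in the analysis on which the trial's conclusion rests. Three things follow.

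- **Precision and chance imbalance.** A change score subtracts baseline with a slope of exactly 1. It does not estimate the slope, so a chance baseline difference between arms is not properly corrected for regression to the mean. It does nothing about age, and over 8 months to 3 years six-month motor gain plausibly depends on age.
- **Choice after the data are seen.** If regression is optional and its covariates are not listed, the adjusted estimate can be selected once results are known.
- **The one covariate named is awkward.** Waitlist children start training six months later by design, so age at time of intervention differs between arms by about six months and, for controls, is not reached before the primary time point.

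In addition, the article could report two treatment effects on one measure: the primary effect and the denominator of the cost-effectiveness ratio.

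**Working it through.** **1. Reproduce the plan's figure.** Inputs (*Sample size*): standardised effect 0.91, power 0.80, significance 0.05. Two-sided is assumed, because sidedness is not stated.
- Normal approximation: n = 2 × (1.96 + 0.84)² / 0.91² = 18.96, so 19 per arm.
- Noncentral t: power is 0.779 at 19 per arm and 0.801 at 20, so 20 per arm.
- Total: 2 × 20 × 1.4 = 56, or 28 per arm.

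The figures reproduce exactly from a two-group comparison without covariates. Power of that comparison at 28 per arm, leaving the design effect out, is 91.7%. All power figures below use 28 per arm on the same basis and take 0.91 to be on the change-score SD, which the article does not state.

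**2. Adjusting for baseline alone.** Let r be the correlation of baseline with six-month GMFM-66 (not given; assumed range) and let the two variances be equal (assumption).
- Change-score variance: 2σ²(1 − r). Residual variance after baseline adjustment: σ²(1 − r²).
- Ratio: (1 − r²) / [2(1 − r)] = (1 + r)/2.

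| r | variance ratio | power, 28 per arm |
|---|---|---|
| 0.5 | 0.75 | 97.1% |
| 0.7 | 0.85 | 95.2% |
| 0.8 | 0.90 | 94.1% |
| 0.9 | 0.95 | 92.9% |

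At r = 0.8 to 0.9 the interval narrows by 1 − √0.90 = 5.1% to 1 − √0.95 = 2.5%. Above 0.9 the gain is nearly nil.

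**3. Adjusting for baseline, age and site (four degrees of freedom).** Let R² be the share of change-score variance they explain (not given; assumed 0 to 0.4). The interval width is multiplied by √(1 − R²).

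| R² | interval narrower by | power, 28 per arm |
|---|---|---|
| 0 | 0% | 91.6% |
| 0.2 | 11% | 96.2% |
| 0.4 | 23% | 99.1% |

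If the covariates explain nothing, the cost is 0.1 percentage points of power (91.7% to 91.6%).

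**4. Chance imbalance in age.** Assume ages uniform over 8 to 36 months.
- SD = 28/√12 = 8.08 months.
- SE of the difference in mean age = 8.08 × √(2/28) = 2.16 months; 95% range ±1.96 × 2.16 = ±4.2 months.
- At an assumed 0.3 points of six-month gain per month of age, the estimate moves by up to ±4.23 × 0.3 = ±1.3 points. Halving or doubling that slope gives ±0.6 or ±2.5.

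The article gives no GMFM-66 SD, so this cannot be set against the expected effect in points.

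**5. Age at time of intervention as a covariate.** Let T = 1 for immediate treatment, τ the treatment effect, b the slope on age at randomisation A, and A* = A + 6(1 − T) the age at intervention. Then

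a + τT + bA = (a − 6b) + (τ + 6b)T + bA*.

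A six-month between-group model using A* would estimate τ + 6b. At b = 0.3 that adds 6 × 0.3 = 1.8 points. Age at randomisation avoids this.

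**6. Link to the economic model.** With baseline as a covariate, regressing the change or the six-month score gives the same group coefficient. The two analyses therefore coincide if covariates, time point and children are the same.

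**The case against.** **The article condenses a fuller protocol, and a SAP may fix the model.** This stands as far as missing detail goes. The point therefore rests on the contrast between two sections of the article: one commits to adjustment of change in GMFM-66, while the other makes it optional for the primary analysis.

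Some stronger readings are tempting but unsupported:

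- **That the primary analysis is unadjusted and ignores baseline and age.** The text never says unadjusted and allows regression with age as its example. A change score uses baseline by subtracting it, and averaging two baseline measurements already reduces measurement error.
- **That the result would be biased.** Under randomisation the change-score comparison is unbiased, and its confidence interval already allows for the imbalance in step 4.
- **That leaving site out invalidates the standard error.** In a simulation of site-stratified allocation of 56 children, the t-test ignoring site had a type I error of 0.049 at the protocol's own intra-cluster correlation of 0.02, and 0.040 and 0.032 at 0.1 and 0.3. The error is conservative, and negligible at 0.02.
- **That the two reported effects will certainly disagree.** The economic section fixes no time point and the primary model may yet be adjusted, so a difference is possible, not certain.
- **That age at time of intervention will distort the primary estimate.** The article does not say it would enter the six-month between-group model; it may be meant for exploratory work.

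**Conclusion.** The concern holds as a choice of analysis that should be improved. It is not an error that biases the trial, and no stated figure becomes wrong. The loss is in precision and in exposure to chance imbalance, together with an unfixed adjustment and a possible mismatch between two effects on one measure.

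The size depends on quantities the documents do not give. From baseline alone the gain is small if the correlation is 0.8 or higher (about 1 to 2 percentage points of power at 0.9 to 0.8). If the three covariates together explain 20 to 40% of the variance of change, the gain is about 4 to 7 points. The case for changing the plan does not depend on the upper end of that range, because the cost when the covariates explain nothing is negligible.

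**What to change.** State in the protocol or SAP that the primary analysis is a linear model of six-month GMFM-66 on randomised group, mean baseline GMFM-66, age at randomisation and site. Specify age at randomisation rather than age at time of intervention. Use the same adjusted model for the effectiveness difference in the cost-effectiveness analysis, and state the time point of that difference; if it is not six months, say so and say why. Report the raw change-score comparison as supportive, and label any further regression exploratory.

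The cost is about a sentence of wording for the primary model, a few words in the economic section, and four degrees of freedom. All covariates are already collected, and neither the sample size nor the visit schedule changes.
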